### Data collection, management and analysis

#### Plans for assessment and collection of outcomes

A study-specific ATT-Heart Data Management Plan, using electronic Case Report Forms (eCRFs), has been developed to describe the main processes and procedures used to ensure consistent and efficient collection and management of all data gathered for the clinical trial.

#### Data management

The ATT-Heart Data Management Plan has been created specifically for the clinical trial. Any study data will be entered in the eCRF platform, which automatically creates a protected audit trail for all data entries and changes.

The CI will act as custodian for the ATT-Heart study data.

Access to the eCRF platform will be password protected and electronic login credentials will only be issued to authorised individuals following the study-specific eCRF training.

#### Data analysis plan

Demographic data and baseline characteristics will be summarised to describe the populations analysed in this study (both all participants and participants administered at each dose level). Response will be reported descriptively based on the per-protocol population. Time to first response will be summarised by Kaplan-Meier curve. Median time to event estimation as well as the associated 95% CI will be reported. All other secondary endpoints will be summarised by rates and corresponding 95% CIs.

Interim safety data will be reviewed after dosing of the first and last patient of each cohort, with interim analyses provided to the Data Monitoring Committee (DMC) in order for decisions related to the next patient cohort to be made. This is particularly in relation to any safety concerns, or DLTs, prior to confirming progression of the dose escalation for the next cohort. In addition, the DMC will be informed of any Serious Adverse Reactions or Suspected Unexpected Serious Adverse Reactions (SUSARs) as they occur. All safety data will be analysed descriptively. Statistical comparisons between patient populations are unlikely to be used, but if needed, a 5% level of significance will be used.

Study data will be pseudo-anonymised and will be stored on a password protected computer at GOSH. Clinical data will be transcribed from the medical notes and source data sheets to the study-specific recording system. All data will be stored in line with UK General Data Protection Regulation and UK Data Protection Act 2018.

#### Clinical trial auditing

The Sponsor is responsible for implementing quality control and quality assurance.

Once study data are entered into the (trial-specific) ATT-Heart eCRF platform and saved, data validation checks will provide the first quality control step to check for completeness and plausibility of any manually‐entered trial data. These programmed edit checks will run online as soon as each data form is saved by the user.

The Sponsor Clinical Trial Co-ordinator will then perform source data verification (SDV) after the automatic validation checks have been completed. SDV will occur as part of monitoring visits to ensure the accuracy of manually entered trial data by the research team by comparing the eCRF data entry against the source data.

#### Harms/safety reporting

Adverse events, including Serious Adverse Events (SAEs) will be recorded from the Screening Visit to the Safety Follow-up Month 12 (after TR006 dosing) study visit. From the Month 12–24 safety follow-up period, only SUSARs will be reported. DLTs will be assessed from Week 0 to Week 4 of the study.

The Sponsor should report all the relevant safety information to the concerned Competent Authority (MHRA) and to the Research Ethics Committee concerned. The Sponsor shall inform all investigators concerned of relevant information about SUSARs that could adversely affect the safety of the study participants. The Sponsor will submit a development safety update report relating to this trial IMP to the MHRA and REC annually.

#### Confidentiality

In order to protect the privacy and identity of ATT-Heart participants, patients who take part in the study will be assigned a unique patient trial identifier on consent/assent (where appropriate). Only investigators and authorised staff at the study centre will be in possession of documents that link patient names to patient trial identifiers (eg, the signed informed assent/consent form(s) and ATT-Heart consent and enrolment log).

#### Access to data

The data used and/or analysed during this study are available from the CI ([name]) on reasonable request. For example, the full protocol and participant-level dataset will be available on request.

### Plans for collection, laboratory evaluation and storage of biological specimens for genetic or molecular analysis in this clinical trial/future use

All laboratory investigations that are required are part of the routine management of heart transplant patients (desirable assessments only required if being collected as part of routine clinical care), except the following additional research samples:

PBMC panel (2 mL).Treg panel (1 mL).Circulating cytokines (3 mL).Alloreactivity (2 mL).Transcriptomic/gene expression (3 mL).

These will be collected at various study visits with a maximum of approximately 11 mL of additional blood per study visit collected from participants for the processing of research samples.

Some of the cardiac biopsy samples that are collected as per routine clinical care will be transferred to labs at GOSH and/or Guy’s Hospital and/or King’s College London for analysis and storage. Additionally, if there are any leftover clinical blood samples (collected as per routine clinical care), these also may be sent to labs at GOSH and/or Guy’s Hospital and/or King’s College London for analysis and storage.

If there are any cells remaining from the TR006 manufacturing process, these may be retained by the study team to further investigate the IMP.

Consent for optional samples will be sought from participants and their parents/guardians using the ATT-Heart Participant Information Sheet(s) and Informed Consent/Assent Form(s).

Samples will either be destroyed at the end of the study or may be used in future research studies with the participant’s consent.

### Clinical trial oversight

#### Trial management group

The trial management group (TMG) is led by [name], the CI for this study. The group will include the CI, statisticians, clinical trial manager and representatives of the other teams involved in the delivery of the trial, including the GMP unit, laboratories and data management. The TMG will be responsible for the day-to-day management of the trial activities and will meet on a regular basis to discuss any trial related activities or issues.

#### Trial steering committee

The Trial steering committee (TSC) will provide advice for the conduct of the trial. It will comprise an Independent Chair and at least two other members. The TSC will provide overall supervision of the trial and ensure that it is being conducted in accordance with the principles of GCP and the relevant regulations. The TSC members will meet on an ad-hoc basis to discuss trial status, recruitment progress and any other relevant issues, and provide recommendations to the TMG/Sponsor.

#### Data monitoring committee

The DMC will be responsible for ongoing monitoring of the efficacy and safety of subjects in the study according to the DMC charter. The DMC charter will detail membership and terms of reference. The DMC members will be independent and supported by the CI, Trial Statistician and Clinical Trial Manager.

In order to ensure patient safety throughout the conduct of the trial, the DMC will review and evaluate accumulated safety data, study conduct and progress. The DMC will make the decisions about the continuation, modification or termination of the study. The recommendations made by the DMC to alter the conduct of the study will be forwarded to the Sponsor for a final decision. The Sponsor will forward such decisions to regulatory authorities, as appropriate.

Outside of the planned reviews, a DMC meeting could be triggered if specific safety events occur (as stated below):

If a DLT is observed in two patients within a dosing cohort.If death of a patient infused with TR006 occurs.Or at any other time deemed necessary by the DMC chair.

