## Methods and analysis

### Study design

This is a phase I, open label, single-centre clinical trial investigating two different dose banding ranges (1–3×10^6^ cells/kg and 5–10×10^6^ cells/kg) of autologous thymus derived Tregs (TR006) in nine paediatric heart transplant recipients. All clinical and patient-facing activity (including dosing) will occur at GOSH in London, UK.

When a suitable organ is available for a recruited study patient (see figure 2), their thymus tissue will be collected during surgery. This tissue will be transported to the GMP Facility at Guy’s Hospital National Health Service (NHS) Foundation Trust and will form the starting material for the IMP production under GMP conditions, as outlined in the manufacturing section below.

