### Intervention description: dose escalation strategy

Participants will receive a 10 mL single dose of TR006 at 1–3×10^6^ TR006/kg or at 5–10×10^6^ TR006/kg.

A single ascending dose design will be followed with groups of three patients in three cohorts. The first cohort of three patients will receive a lower dose of 1–3×10^6^ Tregs cells/kg and if no Dose-limiting Toxicities (DLTs) occur, then the second cohort (of three patients) will be given a higher dose of 5–10×10^6^ Treg cells/kg. The third cohort of three patients will receive the highest tolerated dose of Tregs from the second cohort (up to a maximum of 10×10^6^ Treg cells/kg).

These dose ranges were selected to match what we estimate to be the minimal anticipated biological effect doses based on the ThRIL and ONE study.^17 20^ Of note, the dose escalation schedule in ATT-Heart is more conservative than previous Treg trials conducted in children in Poland,^14^ the USA^16^ and Spain.^21^ However, as this is the first clinical trial in the UK with thymus derived Tregs, our priority is to determine safety of the IMP, as agreed with the Medicines Healthcare products Regulatory Agency (MHRA).

We will monitor biological activity of Tregs in vivo in this study. However, we plan to conduct further dose escalation and formally investigate biological efficacy in a future phase II trial if this trial confirms initial safety in patients and feasibility of manufacturing initial dose ranges.

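### The DLT count that prompts an unplanned DMC meeting restarts with cohort 3, although cohorts 2 and 3 can share the upper dose band

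*Protocol article*

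**What the plan says.** All references are to the protocol article.

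- **Data monitoring committee.** Outside the planned reviews, "a DMC meeting could be triggered if specific safety events occur". The events are two patients with a DLT ("If a DLT is observed in two patients within a dosing cohort"), the death of an infused patient, or the chair's judgement ("Or at any other time deemed necessary by the DMC chair"). The section also says that "the DMC will review and evaluate accumulated safety data".
- **Study design** describes the trial as "investigating two different dose banding ranges": 1–3 and 5–10×10^6 cells/kg.
- **Intervention description: dose escalation strategy** sets three cohorts of three. Cohort 2 moves to the upper band if cohort 1 has no DLT. Then "The third cohort of three patients will receive the highest tolerated dose of Tregs from the second cohort", capped at 10×10^6 cells/kg.
- **Data analysis plan.** "Interim safety data will be reviewed after dosing of the first and last patient of each cohort", and "the DMC will be informed of any Serious Adverse Reactions or Suspected Unexpected Serious Adverse Reactions (SUSARs) as they occur".
- **Primary endpoints** lists DLT types that need not be serious, such as fever and biochemical disturbance, within 4 weeks of dosing.

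**The concern.** The prompt counts by cohort, whereas the exposure it is meant to watch goes by dose. Cohorts 2 and 3 can both be treated in the upper band, so up to six of the nine children may receive it. Two DLTs among those six meet the prompt if they fall in the same group of three, and do not if they are split one and one.

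Other safeguards cover most split patterns. One is left: cohort 3 is open in the upper band after one cohort 2 DLT, its first child has none, and its second has a non-serious DLT that is known before the third is dosed. No planned review follows a cohort's second child, a non-serious reaction is not among those notified to the DMC as they occur, and the count stands at one for that cohort. At stake is whether a stated count draws the DMC's attention to two DLTs in the band before the last child is dosed.

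**Working it through.** **The plan's own figure.** 3 cohorts × 3 children = 9, which agrees with the nine children in the Primary objective. The article gives no DLT rate and no operating characteristic for the prompt, so the DLT rate p is assumed at 5%, 10%, 20% and 30%.

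**Inputs from the article.** Two patients with a DLT within a cohort (Data monitoring committee); cohorts of three, with cohorts 2 and 3 able to share a band (dose escalation strategy); planned reviews after the first and last child of each cohort (Data analysis plan).

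**Further assumptions.** DLTs are independent; cohort 2 has opened; cohort 3 always reopens the upper band; each DLT is known before the next child is dosed; the review after cohort 3's first child takes place before the second is dosed.

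**Patterns.** Number the upper-band children 4 to 9. Before child 9 is dosed, two DLTs in the band without two in either cohort means one among children 4–6 and one among children 7–8: 3 × 2 = 6 patterns. The three with child 7 are met by the planned review after the first child of cohort 3. The three with child 8 meet neither the count nor a planned review.

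**Probability.** Write q = 1 − p.

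- A: exactly one DLT in cohort 2 = 3pq²
- B: child 7 without and child 8 with a DLT = qp
- A × B = 3p²q³

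| p | A | B | A × B |
|---|---|---|---|
| 5% | 0.1354 | 0.0475 | 0.0064 |
| 10% | 0.2430 | 0.0900 | 0.0219 |
| 20% | 0.3840 | 0.1600 | 0.0614 |
| 30% | 0.4410 | 0.2100 | 0.0926 |

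Full enumeration of the 2^6 = 64 DLT patterns in children 4–9 gives the same last column. Column B is the chance once cohort 2 has had one DLT and cohort 3 has opened in the upper band.

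**Sensitivity.** A × B includes serious DLTs, which reach the DMC by notification when judged to be reactions to the product.

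- If half of DLTs were non-serious: 0.3%, 1.1%, 3.1%, 4.6%.
- If the band were also reopened only half the time: 0.2%, 0.5%, 1.5%, 2.3%.
- Cohort 2 opens only if cohort 1 has no DLT. With the same p in cohort 1, A × B × q³ = 0.6%, 1.6%, 3.1%, 3.2% (q³ = 0.857, 0.729, 0.512, 0.343).

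Both halves are assumptions without a source in the article.

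**How often a same-band count would add a prompt.** One DLT in cohort 2 and at least one in cohort 3: 3pq²(1 − q³) = 1.9%, 6.6%, 18.7%, 29.0%, under the same assumptions. By the first cohort 3 child affected:

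- child 7: 3p²q² = 0.0068, 0.0243, 0.0768, 0.1323
- child 8: 3p²q³, as in the table
- child 9: 3p²q⁴ = 0.0061, 0.0197, 0.0492, 0.0648

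Children 7 and 9 together make up about two thirds of the total at each p (for example (0.0243 + 0.0197)/0.0659 = 0.67), and a planned review is due at both points.

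**The case against.** The strongest reply is that nothing in the section is contradicted and that the DMC is already alert. It reviews cohort 2 after its last child, with DLTs as a stated focus, decides knowingly to continue, and reviews again after cohort 3's first child on accumulated data. Only an optional prompt restarts with the cohort; the DMC's knowledge does not. This stands, and it limits the point to a prompt. A reader might infer that the trial lacks a stopping rule or that the DMC would overlook the earlier DLT. The permissive wording of the list and the review of accumulated data do not support that.

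A same band also need not mean a same dose. The upper band is twofold wide, and the cohort 3 dose wording leaves room for a lower dose within it after a cohort 2 DLT. This stands too: a pooled count could join a DLT near 10 with one near 5×10^6 cells/kg, and the DMC would have to weigh that.

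Next, the phrase for a dosing cohort might mean dose level, since Dosing strategy speaks of two groups. That would close the gap. But the dose escalation section uses cohort for each group of three, so the reading is possible and not the natural one. The DMC charter, which is not shown, may also count by dose level.

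Finally, a meeting stays discretionary even when the count is met. A reader might infer that pooling guarantees a review before the last child. It does not, because the article attaches no dosing hold to the prompt.

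**Conclusion.** The point holds as a cheap improvement of low severity, something the sponsor could do. The stated count does not follow dose exposure when cohorts 2 and 3 share the upper band, and one narrow path leaves neither the count nor a planned review to bring a second DLT to the DMC before the last child is dosed. The chair can still call a meeting.

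The size is about 0.6% to 9.3% for assumed DLT rates of 5% to 30%, given that cohort 2 opens, and less after the discounts shown. It is tempting to read these as upper bounds, but the documents do not support that. The planned review is tied only to dosing, while the DLT window runs 4 weeks, so a late DLT in cohort 3's first child could also fall after its review. The figures are illustrative and rest on independence, prompt knowledge of each DLT and reopening of the band. If the charter already counts by dose level, or the sponsor means dose level by its term, only the wording needs aligning.

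**What to change.** Keep the present trigger and extend it: "If a DLT is observed in two patients within a dosing cohort", *or in two patients treated in the same dose band across cohorts*. Add that the DMC chair is told when this count is reached and before the next child is dosed. Without that notice the longer count alone would not secure the chair's attention in time.

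The prompt stays permissive, and the DMC weighs any difference in actual dose within the band. The change is a phrase and a notification line in the protocol and, if needed, the DMC charter, with no extra patients or procedures. The cost is an occasional extra unplanned meeting. The added count would act in roughly 2% to 29% of trials that reach the upper band at the assumed rates, and about two thirds of those occasions coincide with a planned review.

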#### Patient and public involvement

Patients and members of the public have been involved during the design and development of this trial. Paediatric recipients of heart transplants and their parents were consulted about the study topic and relevant age-appropriate literature. They provided detailed feedback (structure, content and wording) on the patient information leaflets, which was incorporated. Furthermore, trial rationale and design were presented to participants of the GOSH Young Persons and GOSH Parents and Carers Advisory Group (in two separate sessions), as well as members of an independent Research Ethics Committee. Positive feedback and enthusiasm for the project was received with valuable feedback on our trial design and patient-facing documentation.

We plan to maintain PPI during the trial by gathering responses to items in questionnaires or surveys exploring the study and treatment experience of the participants and their parents/guardians, which will help us assess the feasibility of retaining participants for the duration of the ATT-Heart study and willingness to join future trials (Secondary objective point 4). Additionally, members of the PPI group will form part of the Data Monitoring and TSCs for continual input during the conduct of the trial.

### Ethics approval and dissemination

The study protocol and related documents have been approved by an NHS Research Ethics Committee (REC), the Health Research Authority and the MHRA for Clinical Trial Authorisation. REC approval for the study was obtained from the South-Central Oxford A Research Ethics Committee on 19-DEC-2024 (REC Reference: 24/SC/0333).

The CI will submit a final report at the conclusion of the trial to the Sponsor and the necessary regulatory bodies within the stipulated timelines. Furthermore, it is intended that the results of the trial will be presented at international conferences and will be submitted for publication in a peer-reviewed scientific journal.
